### Validity and reliability

The questionnaires used in the study (EQ5D, HADS, MFIS, and CAREQOL-MS) have been tested for validity and reliability in studies involving PwMS. Three papers report total HADS scores in PwMS and were considered in the study design of this study [74–76]. The EQ5D quality of life measure is commonly used in the MS population [23], and the MFIS is a standard measurement of fatigue in PwMS [82, 87]. The CAREQOL-MS, a caregiver quality of life survey for those caring for PwMS is also commonly used in this patient population [83, 88]. Satisfaction with healthcare provider care will be measured by the overall mean score of the CSQ completed at the 6-month follow-up visit. The CSQ is a self-administered tool with 18 questions; it measures 3 factors of the healthcare provider interaction: (1) professional aspects; (2) depth of patient relationship with provider; and (3) perceived length of consultation. The higher the score indicates a higher level of patient satisfaction [73, 84].

To reduce possible biases in the study, we will use objective measures to examine the effects of NP-led care in comparison to standard care. It is important that all participants will be offered an opportunity to see a NP either within 4 weeks for the intervention arm or at 6 months for the control arm. Thus, those participants randomized to the control arm will be provided with an appointment with the NP at 6 months. Then, 12-month follow-up of all participants will be conducted, to see if the timing of intervention makes a difference over the long term.

### Ethical considerations

The research protocol was reviewed and approved by the Health Research Ethics Board of the University of Alberta (approval number Pro00069595), initially on March 30, 2017, with protocol modification to version 2 approved on Jan 11, 2018. PwMS will be able to be referred to the NP by community neurologists and family physicians outside of participating in the study if they decline to participate in the study.

### Data security and storage

Electronic data will be collected and stored using the RedCap secure website, housed behind the Faculty of Medicine and Dentistry firewall and secure server. Data will be stored under secure conditions for 10 years at EPICORE Centre, in accordance with EPICORE Centre’s standard operating procedures. The questionnaires and consent forms will be completed electronically by the participants, participants will be offered paper copies if required. Electronic files will be kept on a secure server (Faculty of Medicine and Dentistry firewall) with password protection. Access will be limited to directly involved personnel. Paper copies will be kept in locked cabinets within the EPICORE Centre as according to their standard operating procedures. A master list of participant name and personal healthcare number with associated research number will be kept in a separate locked cabinet. Once secondary outcome blinded analysis has been completed, it will be destroyed. The research patient data will also be kept in a separate locked cabinet. Both of these cabinets are located in a locked room with limited access to research personnel only. Electronic files will be kept on a secure server (Faculty of Medicine and Dentistry firewall) with password protection. Access will be limited to those directly involved in this study (e.g. statistician, research assistant, and database manager). The electronic data information will be deleted after the 7-year post study completion requirement has been completed.

### Data monitoring

There will be an interim analysis completed after the 3-month follow-up has been completed. The study involves PwMS completing validated surveys of their depression and anxiety scores which will be reviewed routinely by the NP and neurologist. If a PwMS depression and anxiety score falls drastically, the NP or neurologist will follow up with the patient and provide any necessary care or referral. Quality assurance of the data will be performed by the data entry researcher and the project manager for the trial. Any and all amendments will be communicated to all investigators, research ethics office, and the participants. The study investigators will make the final decision to terminate the trial if needed. Since this a smaller, single-centre study, we do not have plans for independent audit of trial conduct.

Electronic data will be collected and stored using the RedCap secure website which is housed behind the Faculty of Medicine and Dentistry firewall and secure server. Paper copies will be kept in locked cabinets within the EPICORE Centre as according to their standard operating procedures. Participants will be sent a reminder by the EPICORE Centre team to complete the questionnaires at baseline, 3 months, 6 months, and at 12 months to encourage participants to complete follow-up visits. The first or last observation will be carried through to account for any missing data during the data analysis.

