Our research question is to evaluate whether the add-on care by a NP is superior for PwMS compared to their usual medical care in a generalist medical setting of general neurologist and/or family physicians. This study aims to evaluate the add-on effects of NP-led care for PwMS on their depression and anxiety levels compared to ‘usual care’ (community neurologists’ care or family physician). We hypothesize that PwMS whose care is managed by an NP would have less depression and anxiety from baseline (as measured by the Hospital Anxiety and Depression Scale—HADS) at 3 months [47, 74–76]. The objectives of this study are
To evaluate the add-on effects of NP-led care for PwMS on their depression and anxiety levels at 3, 6, and 12 months compared to ‘usual care’,To measure quality of life for PwMS and their caregivers and fatigue levels,To evaluate the number of outpatient healthcare visits and phone calls, andTo measure patients’ satisfaction of the care provided in both groups.

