PwMS will be included at baseline irrespective of whether they have depression at study entry, or long-term depression, or depression already managed with pharmacotherapy or therapies. This is because of studies suggesting that PwMS scoring high on depression levels often have not been previously identified as having depression or anxiety within a cohort [28], and that even those with previously identified depression or anxiety are often undertreated [45]. Baseline testing will be done for all participants; therefore, participants will become their own controls, as to outcomes on change in levels of depression and anxiety over 3 months, and then 6 months in addition to other quality of life outcomes. Therefore, we will see if the NP involvement and the consequent additional supports, counseling, etc., provides a change over time from baseline depression and anxiety levels. We postulate that depression and anxiety may be most responsive to the holistic approach of an NP over the short term in comparison with other quality of life measures [30, 47]. The primary outcome of depression and anxiety score changes at 3 months was chosen as the primary outcome due to published studies examining efficacy of interventions for depression and anxiety for PwMS carrying out active intervention strategies ranging in duration from 6 to 16 weeks (median 12 weeks), demonstrating overall efficacy in mainly depression and suggested efficacy in anxiety by a systematic review and meta-analysis [47].

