### Individuals who will perform the interventions

The NP will deliver care to those participants randomized to the NP-led care arm during the 6 months of study duration in addition to participants’ regular healthcare providers, while the participants’ regular community neurologists and family physicians in addition to their registered nurses will deliver care to those participants in the usual care arm. There will be one NP participating in the study. She was hired as a general NP, with no specialized skills in MS. However, before moving into the community neurologist environment, she will be mentored and trained for a 3-month period by the MS clinic NP, who has over 6 years of experience in MS, and MS clinic subspecialist neurologists. All the education resources, treatment approaches, interventions, and referral patterns from the MS clinic will be shared with the NP who will be participating in the study. One of the MS clinic neurologists (primary author of this paper, PS) and the MS clinic NP will be continuing to mentor and support this NP through the study. After training at the MS clinic, the study will start after the NP has worked in the community setting for 1 month. This will allow her to orient herself, to understand community neurologists’ practices and approaches, and amalgamate with what she has learned from the MS clinic. This is being done to ensure that the NP involved in the study is comfortable and supported in her approach to supporting PwMS, and to minimize learning curves or experience effects through the study. An information session for the community neurologists and the NP will be set up prior to initiating the study, outlining the study protocol. There are no specific requirements or training for family physicians or community neurologists to have their patients participate in the study. This will ensure their ‘usual’ practice of how they treat PwMS. The administration of surveys and outcome assessments are being done by EPICORE Centre and sent to participants directly. Therefore, no training needs to be done by the NP, community neurologists, or family physicians in this study.

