### Control arm (usual care arm)

PwMS who are randomized to the usual care arm (community neurologist or family physician and registered nurses) will be contacted by the NP to be scheduled for an NP appointment at 6 months after study conclusion. Thus, every PwMS is given the opportunity to access NP care after their involvement in the study has concluded. During the 6-month period, patients randomized to the control group will receive usual care from community neurologists or family physicians and MS registered nurses. The care will be delivered according to standard practices, and follow-up visits will be conducted according to the various clinical practices of the neurologists’ or family physicians’ clinics. For those in the usual care arm, the EPICORE Centre’s research team will contact the participant +/− caregiver about the completion of questionnaires at the appropriate timepoints. The participant diary will be collected by the NP when the participant in the usual care arm has finished the study and is offered a follow-up visit with the NP outside of the study. If family physicians wish to have more urgent patient assessments, they will be offered the additional opportunity of referring the patient to a community neurologist or a NP outside of the study if they feel that the patient cannot wait 6 months for MS specialized care; these patients will also be excluded from being involved in the study.

Participants are able to initiate contact with their usual community neurologist and/or family physician in either arm of the study, throughout the study as they need. Participants will continue to be followed by their family physicians and regular community neurologists during the study, in either arm. For those in the NP-led care arm, they will receive additional care by the NP during the 6 months of the study duration.

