A longer-term follow-up will be conducted at 12 months to evaluate the long-term differences of the 6-month intervention in change of the patient-reported outcome measures (HADS, MFIS, EQ5D, and CAREQOL-MS). By then, all participants would have seen the NP, and the goal of the late follow-up would be to see if there was (1) long-term impact of the 6-month NP intervention (from those in the original intervention group), and (2) to check the larger patient number impact of the NP intervention upon those within the control group.

If participants score very low or severe on their scales around anxiety, depression, fatigue, quality of life, and/or their caregivers score as very low on their questionnaire, their community neurologist and/or family physician will be contacted to see the participant on an urgent basis.

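### The safety trigger on depression and anxiety scores is worded in the wrong direction: on HADS a steep fall is improvement

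*Protocol article*

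**What the plan says.** The Data monitoring section describes participants' "depression and anxiety scores which will be reviewed routinely by the NP and neurologist". It then sets the action rule: "If a PwMS depression and anxiety score falls drastically, the NP or neurologist will follow up with the patient", with care or referral as needed. It gives no threshold and names no arm.

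The Outcomes section holds a second rule, based on the level of a score and not on its change: "If participants score very low or severe on their scales around anxiety, depression, fatigue, quality of life" (caregivers' scores are covered too), then "their community neurologist and/or family physician will be contacted to see the participant on an urgent basis". The NP is not named there.

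Two places show which direction is good. The Background hypothesis is that "PwMS whose care is managed by an NP would have less depression and anxiety from baseline", measured by HADS. The Population section justifies broad entry on the ground that "PwMS scoring high on depression levels often have not been previously identified as having depression or anxiety".

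On who receives NP care, the section on individuals performing the interventions says "The NP will deliver care to those participants randomized to the NP-led care arm during the 6 months of study duration". The Control arm section says "patients randomized to the control group will receive usual care from community neurologists or family physicians" and MS registered nurses, for the 6-month period. The Dissemination section places the controls' NP appointment at the end of the study.

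**The concern.** A monitoring rule should fire when a participant gets worse. This one, read as written, fires when a participant gets better. It is also the only rule in the article that responds to a change in score. The Outcomes rule needs a score that is already extreme, so a sharp deterioration that stops short of severe falls between the two.

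The secondary matter is who responds. The NP is the randomised intervention. A rule that has the NP review scores and offer care without naming an arm leaves room for a control participant to receive NP care during the comparison period. If that happened, it would tend to narrow the difference between arms at 6 months.

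**Working it through.** The rule contains no figure to reproduce, so the check compares texts and then counts the time and people that could be affected.

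**Direction**

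1. The depression and anxiety instrument is HADS (Data collection; Outcomes).
2. The hoped-for effect on HADS is less depression and anxiety (Background).
3. High depression scores mark the unrecognised cases (Population section). This is a general statement about a cited cohort and does not name HADS, but it agrees with step 2.
4. So a fall in HADS is improvement and a rise is worsening. The stated trigger is a fall.

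**What each rule catches, read literally**

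| Course on HADS | Data monitoring rule | Outcomes rule |
|---|---|---|
| Steep fall (improvement) | fires | fires only if the score counts as very low |
| Sharp rise into the severe range | does not fire | fires |
| Sharp rise that stays below severe | does not fire | does not fire |

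The last row is the gap.

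**Exposure from the unstated arm limit**

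Inputs: HADS readings at months 0, 3, 6 and 12 (Data collection); primary outcome at month 3 and secondary HADS outcomes at month 6 (Outcomes); planned enrolment of 220 (Sample size and power analysis) at 1:1 (Randomization section).

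- A change needs two readings, so the rule can first act on the month-3 reading, which is itself the primary reading. Exposed time before the primary: 0 of 3 months.
- Exposed time before the 6-month outcomes: 6 − 3 = 3 of 6 months.
- Controls at planned enrolment: 220 / 2 = 110.

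The last two are ceilings. The article gives no rate at which alerts arise and no rate at which the NP, and not the neurologist, would answer them. Any dilution or power figure would rest on an invented share of controls, so none is offered.

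**The case against.** The strongest reply on direction is that nobody would act on the literal words. The same sentence offers necessary care or referral, which makes sense only for worsening, and the Outcomes section uses very low in the same loose sense of doing badly. That stands as an account of intent and keeps the point minor. It does not make the sentence right, and the severe trigger elsewhere closes only part of the gap. It is also true that the article never states how HADS is scored. The direction is inferred from the hypothesis and the general remark on high scores, and that inference is secure.

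On the arm question the reply is better. The sections on who delivers care, on the control arm and on post-trial care keep NP care in the intervention arm for 6 months. Read with them, the pairing of NP or neurologist can mean the NP in one arm and the neurologist in the other. The Limitations section admits that providers used in either arm cannot be controlled, and family physicians who want urgent assessment can refer outside the study, with the patient then excluded. So a reader might infer that the monitoring rule contradicts the control-arm definition; it does not. What remains is an ambiguity: the rule names no arm, and the article says it has no methods to ensure fidelity to either arm.

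A reader might also infer that worsening participants went without follow-up, or that the primary comparison was contaminated. Nothing in the article shows the first, and the timing of the readings rules out the second for this rule.

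**Conclusion.** The direction error holds, with high confidence. As written, the trigger describes improvement, and a sharp worsening below the severe range meets no stated rule. It is minor, because the intent is plain and the most extreme scores are covered elsewhere.

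The arm point holds only as a request for clarification. The 3-month primary is not exposed, on the assumption that HADS is read only at the scheduled times. The 6-month secondaries could in principle be affected within the ceilings above, but no effect on them is shown and none can be quantified from the article.

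**What to change.** In Data monitoring, replace the falling-score trigger with a marked rise (worsening) in HADS-A or HADS-D. The Outcomes rule can stay as it is.

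In the same place, state that alerts for control participants before month 6 go to the community neurologist or family physician, as the Outcomes rule already provides.

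The Trial status section puts the last 6-month visit in November 2020, so the arm limit can no longer change conduct. Report instead which rule was applied in practice and, where records allow, how many controls received clinical NP care before month 6. Count clinical care only: the Control arm section already has the NP contact every control to schedule the later appointment, and counting those calls would mislead. The article describes NP charting only for the intervention arm, so the records may be incomplete and the report should say so. Any check should precede destruction of the list linking research numbers to healthcare numbers, described under Data security and storage and under Confidentiality.

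The corrected trigger can still serve any 12-month questionnaires not yet returned.

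The cost is two wording changes and one look through at most 110 control records at planned enrolment. No new participant data are needed, and no outcome analysis changes.

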### Confidentiality

Initially, identifying information will be collected to allow the research assistant to look for data required to assess for secondary outcome information (i.e. admission to hospital and/or emergency visits, MS relapse, infection or adverse events from medication). Participants will be offered to complete the questionnaires via secure internet website; however, some may prefer a paper copy in which case the participant’s full address and phone number may be required for participants that opt for paper questionnaires to be mailed to them for follow-ups. Therefore, depending on patient preference, we will collect the email or postal addresses for reminders to be sent to fill out the questionnaires.

Patients will complete diaries of phone calls and visits to GP, neurologist, emergencies, HealthLink, and other healthcare professionals (such as physiotherapists, occupational therapists, pharmacists, dieticians, homecare, social workers). This information will be de-identified once collected.

Identifying information will be removed once the above data are obtained. Charts will be reviewed weekly to ensure all data are complete, and all identifying information will be removed by a research assistant and coded with only a research number. A master list coordinating research numbers and patient’s healthcare number will be kept separate from patient data in a separate locked cabinet which will be retained until the end of the study. At the conclusion of the study, this list will be destroyed.

### Dissemination, ancillary, and post-trial care

The longitudinal care for participants will continue throughout the study by their community neurologists and/or family physicians, in addition to the NP care in the intervention arm, as an add-on member of the care team, and described previously. Those in the control arm of ‘usual care’ will have an appointment with the NP at the end of the study, to receive the ‘add-on’ care from the NP for the 6 months after study completion, to ensure that every participant has access to seeing the NP. The results of this study will be shared with Alberta Health Services in consideration of their continuing to fund the position for supporting community neurologists in an outreach model going forward after the study. The hope is that the NP will continue in the outreach model established during the study. We are planning to have the NP position continue to operate within a 6-month intervention period, followed by referral of the PwMS back to their community neurologists and/or family physicians. This will enable the NP to take new patients over time, and not saturate the NP practice with long-term follow-ups. PwMS will always have the option of being re-referred back to the NP for another 6-month period.

This randomized control trial will be published once data analysis has been completed and all investigators will be invited to contribute to the manuscript. A copy of the publication and findings will be provided to the participants. At this time, there are no plans or arrangements for data sharing. We plan to disseminate the results at the European Committee for Treatment and Research in Multiple Sclerosis (ECTRIMS) conference, present to the Alberta MS Research Network, and to publish outcomes of the study in a peer-reviewed journal.

## Discussion

This study will evaluate the effects of an NP-led care intervention on depression and anxiety levels in PwMS and their informal caregivers. The evidence gained from this study will provide information on how NPs can enhance the care and potentially resolve the identified unmet needs for PwMS when introduced as part of a multidisciplinary team approach for general neurologists working in a distributed community setting.

To our knowledge, there have been no studies examining the add-on intervention of NP-led care provided to PwMS in a prospective, randomized, and controlled clinical trial. Findings of this study will contribute to ways in which the multidisciplinary care for PwMS and their caregivers could be enhanced by the addition of a specialized NP. This study has the potential to provide an additional healthcare service available to PwMS to assist them in managing their complex disease, to improve their quality of life, and to aid community neurologist practices in care delivery to PwMS outside of tertiary MS clinic settings.

